# Improving mental health in chronic care in general practice: study protocol for a cluster-randomised controlled trial of the Healthy Mind intervention

**DOI:** 10.1186/s13063-024-08115-8

**Published:** 2024-04-23

**Keywords:** Diabetes mellitus, Type 2, Heart diseases, Chronic disease, Mental health, Psychosocial intervention, Problem-solving therapy, Randomised controlled trial (publication type), General practice, Primary healthcare, General practitioners, Nurses

## Abstract

**Background:**

Mental health issues are common among patients with chronic physical conditions, affecting approximately one in five patients. Poor mental health is associated with worse disease outcomes and increased mortality. Problem-solving therapy (PST) may be a suitable treatment for targeting poor mental health in these patients. This study protocol describes a randomised controlled trial of the Healthy Mind intervention, a general practice-based intervention offering PST to patients with type 2 diabetes and/or ischaemic heart disease and poor mental well-being.

**Methods:**

A stepped-wedge cluster-randomised controlled trial with 1-year follow-up will be conducted in Danish general practice. At the annual chronic care consultation, patients with type 2 diabetes and/or chronic ischaemic heart disease will be screened for poor mental well-being. Patients in the control group will be offered usual care while patients in the intervention group will be offered treatment with PST provided by general practitioners (GPs) or general practice staff, such as nurses, who will undergo a 2-day PST course before transitioning from the control to the intervention group. The primary outcome is change in depressive symptoms after 6 and 12 months. Secondary outcomes include change in mental well-being, anxiety, and diabetes distress (patients with type 2 diabetes) after 6 and 12 months as well as change in total cholesterol levels, low-density lipoprotein (LDL) levels, and blood glucose levels (patients with diabetes) after 12 months. Process outcomes include measures of implementation and mechanisms of impact. We aim to include a total of 188 patients, corresponding to approximately 14 average-sized general practices.

**Discussion:**

The Healthy Mind trial investigates the impact of PST treatment for patients with chronic disease and poor mental well-being in general practice. This will be the first randomised controlled trial determining the effect of PST treatment for patients with chronic diseases in general practice. The results of this study will provide relevant insights to aid GPs, and general practice staff manage patients with poor mental well-being.

**Trial registration:**

ClinicalTrials.gov NCT05611112. Registered on October 28, 2022.

## Introduction

### Background and rationale {6a}

Type 2 diabetes (T2D) and chronic ischaemic heart disease (CHD) are two of the most prevalent chronic diseases affecting approximately 8% of the global population [1, 2]. Poor mental health is common in these patient groups; psychological comorbidities such as depression and anxiety affect approximately one in five patients [3–5]. In addition to this psychological burden, poor mental health is also associated with reduced self-care activities and medication adherence [6, 7], leading to worse disease outcomes and increased mortality [4, 6, 8–10]. A comprehensive approach addressing both physical and mental aspects is recommended in routine disease management of T2D and CHD, which is mainly undertaken in primary care settings like general practice [11, 12]. General practice, with a patient-centred approach and an established provider-patient relationship, is an optimal environment for early detection and treatment of mental health issues. Additionally, implementing interventions in primary care settings may increase accessibility for vulnerable patients with, e.g., low socioeconomic status and low health literacy. Consequently, interventions aiming to improve mental health in patients with T2D and CHD could ideally take place in primary care settings.

An example of such an intervention is problem-solving therapy (PST), which is an evidence-based and effective treatment for mental health issues like depression and anxiety [13, 14]. Following a relatively short training period, healthcare professionals in primary care can deliver PST [15]. Moreover, due to the tangible and comprehensible nature of PST, it is an easily accessible treatment especially for vulnerable patients. To our knowledge, PST has not previously been integrated and evaluated in chronic care management in general practice.

Building on the PST approach, we developed the Healthy Mind intervention offering PST to patients with T2D and/or CHD and concurrent poor mental well-being in general practice. In a small-scale feasibility study, the Healthy Mind intervention was found to be well-suited for the general practice setting and was positively received by both patients and healthcare providers [16]. This paper describes a stepped-wedge cluster-randomised controlled trial of the Healthy Mind intervention.

### Objectives {7}

The overall aim of the trial is to evaluate the impact of the Healthy Mind intervention using the PST approach in general practice in patients with T2D and/or CHD and poor mental well-being.

The study aims to:Evaluate the effect of PST on mental health outcomes defined as depressive symptoms, symptoms of anxiety and diabetes distress (for patients with T2D) and general mental well-beingEvaluate the effect of PST on somatic disease outcomes, defined as cholesterol levels and blood glucose levels (for patients with diabetes)Evaluate the process outcomes, including measures of implementation and mechanisms of impact

### Trial design {8}

The study is conducted from November 1, 2022, to January 16, 2024, with follow-up after 6 and 12 months. The design is a stepped-wedge cluster-randomised controlled trial with 1-year follow-up (Fig. 1). General practices are randomised into two clusters. Initially, all participating general practices act as the control group. After 4 months, healthcare professionals in cluster 1 undergo a 2-day PST course, following which they transition to the intervention group and begin offering the intervention to eligible patients. Healthcare providers from cluster 2 attend the PST course after 8 months and will subsequently be part of the intervention group.

**Fig. 1 Fig1:**
[figure not shown]
The stepped-wedge cluster-randomised trial design

## Methods: participants, interventions, and outcomes

### Study setting {9}

The study setting is Danish general practice. The Danish healthcare system is primarily tax-financed, and residents have free and equal access to general practice services. General practitioners (GPs) are self-employed, working on contracts for the public funder and offer services in their practices within the frames of a national agreement with Danish regional authorities that details which services are offered in general practice and how these are reimbursed. Nurses and other healthcare professionals (e.g. midwives, healthcare assistants) are frequently employed and trained to conduct independent consultations, including chronic care consultations in general practice [17]. In this paper, these healthcare professionals are referred to as “general practice staff”, while the term “healthcare professional” refers to both GPs and general practice staff. Currently, reimbursement is provided for up to seven 30-min talk therapy sessions per patient over a 12-month period. However, only sessions provided by GPs are remunerated [18].

Patients with T2D and CHD are typically offered annual chronic care consultations provided by either the GP or trained general practice staff. National and international guidelines on disease management encourage healthcare professionals to pay attention to psychological symptoms, but they do not offer specific recommendations on how to identify and manage mental health issues [11, 12]. Typically, annual chronic care consultations focus on specific diseases and lifestyles and less on mental health. When mental health issues are recognised, patients may be offered talk therapy, medication, or referrals to psychologists or psychiatrists.

A list of participating general practices can be provided upon request by the corresponding author.

### Eligibility criteria {10}

The following are the inclusion criteria:Above 18 years of ageDiagnosed with T2D and/or CHDAttend annual chronic care consultationsPoor mental well-being, defined as a WHO-5 Well-Being Index score < 50 points [19]

The following are the exclusion criteria:Severe mental illness (active psychosis, suicidal mental state, or dementia)Unable to understand, read, and write Danish

All general practices in the Central Denmark Region are eligible (*n* = 349). Participating healthcare professionals are GPs and general practice staff with experience in conducting independent consultations.

### Who will take informed consent? {26a}

The healthcare professional delivering the annual chronic care consultation will deliver both oral and written information about the study and obtain informed consent from eligible participants.

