#### Sample size {14}

The sample size was calculated according to the following assumptions: We expect 20% of patients with T2D and/or CHD who attend annual chronic care consultations to decline participation or be excluded from the study. We expect 15% of participating patients to report reduced mental well-being (WHO-5 score < 50 points), and 20% of patients participating in the study are expected to be lost to follow-up after 12 months. The intraclass correlation coefficient (ICC) is conservatively estimated at 0.05, reflecting a realistic expectation that a mental outcome is likely to show a larger dependence on the individual general practice than somatic outcomes, where an ICC of 0.01 is often applied. To achieve a significance level of 5% and a power of 90%, the study is required to include a total of 188 patients.

In Denmark, the size of a general practice depends on its number of practice capacities. Each general practice capacity accommodates approximately 1600 patients, with an average of 2.5 practice capacities per practice. Based on these assumptions, we need to include at least 35 practice capacities (corresponding to 14 average-size general practices) to be able to include 188 patients over a 1-year study period.

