##### Recruitment of patients

Enrolment of patients relies on the general practices to systematically recruit patients at the annual chronic care consultations. The research team will take a number of initiatives to support the workflow of patient recruitment in each general practice. Prior to commencing the study, initial online meetings will be held between two members of the research team and one GP (practice owner) from each general practice to map the staff composition, current chronic care management, and workflow. Together with the GP, the research team tailors a plan for the management of patient recruitment in each individual general practice. Immediately before the study commencement, a visit is paid to each general practice to inform healthcare professionals and administrative staff about the study and facilitate the implementation of the tailored recruitment plan. One healthcare professional from each general practice is appointed the study contact person and study champion, responsible for patient recruitment and implementation of the intervention. Subsequently, videos demonstrating how to provide oral and written information to patients will be distributed to general practices. Throughout the study period, monthly newsletters are forwarded to the participating general practices with general information about the study and individual statistics regarding patient enrolment and number of conducted PST sessions during the intervention period. Patient recruitment is monitored weekly by the research team and champions are promptly contacted by e-mail, telephone, or a visit in case recruitment rates decline, to explore the underlying reasons and support further recruitment.

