#### Concealment mechanism {16b}

Due to the nature of the intervention design, concealment is not possible.

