### Assignment of interventions: blinding

#### Who will be blinded {17a}

Due to the nature and design of the intervention, blinding is not applicable. To avoid a potential impact on the healthcare providers’ professional behaviour, they only receive cursory information about PST during the control period.

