#### Plans to promote participant retention and complete follow-up {18b}

General practices receive remuneration for providing information (written and oral), screening eligible patients and completing PST sessions. Remuneration will match the standard remuneration for equivalent services. This incentive will facilitate continuous patient recruitment and delivery of the intervention.

Moreover, healthcare providers are encouraged to monitor patient attendance and ensure that new PST sessions are scheduled upon cancellation or non-attendance.

The number of questionnaire items is kept at a minimum to prevent item attrition, and both electronic and paper questionnaires are available.

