## Discussion

This study will evaluate the impact of providing PST in general practice to patients with T2D and/or CHD and concurrent poor mental well-being. The chosen stepped-wedge cluster-randomised controlled trial design offers practicality and enhances data collection. Firstly, all general practices are guaranteed inclusion in the intervention arm, easing the recruitment process. Secondly, comparison between the two groups will be affected to a minimum by contextual factors, since the general practices and the healthcare professionals are identical. Thirdly, healthcare providers’ motivation to participate in the study during the control period may increase, knowing they will later transition to the intervention phase. Fourthly, cluster-level randomisation helps prevent contamination arising from treatment spillover.

Further, the embedded mixed methods process evaluation offers an in-depth understanding of how the intervention works and for whom. This comprehensive approach provides crucial insights for future implementation and valuable learning points.

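### Patients are recruited by professionals who know the practice's current phase, so the mix entering before and after the switch can differ, and having the same practices and staff in both phases does not prevent that

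*Protocol article*

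**What the plan says.** Randomisation is at practice level (Sequence generation {16a}). Patients come in afterwards: "Enrolment of patients relies on the general practices to systematically recruit patients at the annual chronic care consultations" (Recruitment of patients). The professional delivering that consultation "will deliver both oral and written information about the study and obtain informed consent from eligible participants" (section {26a}). On concealment: "Due to the nature of the intervention design, concealment is not possible" (section {16b}). On blinding: "Due to the nature and design of the intervention, blinding is not applicable" (section {17a}); the same section adds that staff hear little about PST during the control period.

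Trial design {8} moves one group of practices to the intervention after 4 months and the other after 8, each following a 2-day PST course. On payment, section {18b} states: "General practices receive remuneration for providing information (written and oral), screening eligible patients and completing PST sessions". It adds: "This incentive will facilitate continuous patient recruitment and delivery of the intervention".

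The Discussion argues that "comparison between the two groups will be affected to a minimum by contextual factors, since the general practices and the healthcare professionals are identical". The four limitations that follow are the difficulty of recruiting practices, practices' prior interest in mental health, lack of blinding, and the effect of screening on control patients. Differential entry of patients is not among them.

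**The concern.** When patients are recruited after their cluster's condition is known, randomising clusters does not make the patients comparable. At the switch the same professional goes from having little knowledge of PST and nothing new to offer, to having been trained and having a treatment available. Whom that person approaches, how the study is presented and who agrees may all change.

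The contrast in PHQ-9 change could then mix the effect of PST with a difference in who was enrolled. Random effects for practice and patient do not remove this. The listed covariates (age, gender, socioeconomic status) deal only with those measured differences. Motivation and expected course are not among them.

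The article is also unclear on when consent is taken relative to the WHO-5 score. The order matters because willingness to receive PST could influence entry more directly if consent came after a positive screen.

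**Working it through.** **1. What stays fixed at the switch and what does not.** The practice, the staff, the WHO-5 cut-off and the short list of exclusions stay the same. The recruiter's knowledge of the phase, PST training, the availability of PST and the PST-session fee change. Payment for information and screening carries no phase restriction, so only the session fee is specific to the intervention.

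**2. Order of consent and score.**
- Section {26a} takes consent from eligible patients, and Eligibility criteria {10} includes a WHO-5 score below 50. Read literally, consent follows the score.
- Sample size {14} has 20% of attenders declining or being excluded, and then says: "We expect 15% of participating patients to report reduced mental well-being". Participation precedes the score.
- Section {18a} registers sex, age and diagnosis for patients above 50, and the first note to Table 1 says that only those below 50 proceed. Both fit consent before the score. The rows of Table 1 settle nothing, since consent and WHO-5 share the baseline column.

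The weight of the text favours consent first, and section {26a} is out of line with it.

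**3. Size of the group open to influence, on the plan's own figures.** Attenders needed: 188 / (0.80 × 0.15) = 1,567. Expected to decline or be excluded: 0.20 × 1,567 = 313. If 15% of these would also score below 50 (an assumption), that is 0.15 × 313 = 47 patients, against 188 enrolled. How they divide between phases is not stated.

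**4. How much of the comparison is concurrent.** Assume equal recruitment and two equal groups of practices. Both conditions run side by side only in months 4 to 8, which is 2 × 4 = 8 group-months.
- Over the 1-year study period in Sample size {14}: 8 / 24 = 33%.
- Over 1 November 2022 to 16 January 2024, about 14.5 months: 8 / 29 = 28%.

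The remaining 67% to 72% of recruitment falls when all practices are in the same condition. Much of the contrast is therefore before versus after the switch within a practice, which is where recruitment behaviour can change.

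**5. Scale only, on assumed selection.** Suppose PST has no effect, 188 × 0.80 ≈ 150 patients are analysed, and half are in each condition. Let a share f of intervention patients have an expected change that differs by δ SD. Then bias b = f × δ, SE = √(1/75 + 1/75) = 0.163 SD, and two-sided type I error = 1 − Φ(1.96 − b/SE) + Φ(−1.96 − b/SE). The last column inflates the variance by a parallel-cluster design effect with ICC 0.05 and 14 practices: 1 + (150/14 − 1) × 0.05 ≈ 1.49.

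| f | δ (SD) | b (SD) | Type I error | With design effect |
|---|---|---|---|---|
| 0.10 | 0.5 | 0.05 | 6.1% | 5.7% |
| 0.20 | 0.5 | 0.10 | 9.4% | 7.9% |
| 0.30 | 0.5 | 0.15 | 15.1% | 11.7% |
| 0.20 | 1.0 | 0.20 | 23.2% | 17.1% |
| 0.30 | 1.0 | 0.30 | 45.1% | 32.6% |

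Neither f nor δ comes from the article. The error rates are the same if the bias runs against PST.

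**The case against.** The plan limits discretion more than a bare description of the risk suggests. All attenders are to be screened, the instrument is patient-reported with a fixed cut-off, and the exclusions are narrow and do not include suitability for PST. Recruitment is monitored weekly. Reach is taken from monitoring records. The intention-to-treat analysis already keeps enrolled patients who refuse PST. All of this stands, and it makes the risk smaller. It does not put identification or consent with someone unaware of the phase, and section {18a} describes no register of patients not approached or declining.

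A reader might infer that the recruiting professional is personally paid for each patient steered to PST. The text does not say so. Payment goes to practices at standard rates and also covers information and screening, and GP talk therapy is already reimbursed outside the trial. Only staff-delivered sessions are a new source of payment. Nor must the person taking consent be the one who gives PST, which may come from the trained GP or from staff.

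A reader might also infer that patients unwilling to have talking treatment drop out before consent in the intervention phase only. That needs consent after a positive screen, the less supported reading.

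Finally, the Discussion sentence is about contextual factors and makes no claim about patient mix. It is incomplete rather than wrong, so it needs qualifying and not deleting.

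**Conclusion.** The concern holds as an unacknowledged route to selection, narrowed but not closed by universal screening. Recruiters know the phase, most recruitment time is not concurrent between conditions, and neither the same-practice argument nor the stated covariates deal with a change in who enters.

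The article does not support saying that selection occurred, that it favours PST, or that it has a particular size. The error rates above rest wholly on assumed values. The 28% to 33% concurrent share rests on equal recruitment and equal groups. The figure of 47 assumes that those who decline or are excluded score below 50 as often as participants do.

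The consent wording is a smaller matter: section {26a} sits badly with Sample size {14}, section {18a} and the note to Table 1, and should be aligned with them. Recruitment was due to end in January 2024, so what remains useful lies in analysis and reporting.

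**What to change.** 1. State one order for both phases (consent, then WHO-5 registered in the database, then the phase-specific offer), correct section {26a} to match, and report the order that practices actually used.
2. Using the screening data described in section {18a}, pre-specify a comparison by condition and enrolment period of the number screened per practice capacity per month, the percentage below 50, and age, sex and diagnosis.
3. Add an analysis of the primary outcome adjusted for screening WHO-5 score and diagnosis. If yield or mix shifts at the switch, report the effect as open to selection.
4. Qualify the Discussion statement: shared practices and staff limit contextual differences but not differences in who is recruited. Add differential recruitment to the limitations.

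The cost is one table, one extra model and a few sentences, with no new data collection. The limits should be stated with it. Adjustment covers measured differences only and not motivation. Unless monitoring records hold more than the article describes, the table will also not show refusals directly.

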### Additional consent provisions for collection and use of participant data and biological specimens {26b}

No additional consent provisions are necessary and there are no ancillary studies.

